### Analysis of the main effectiveness results

11.1

The purpose of this experiment is to evaluate the difference in treatment efficacy between the experimental group (eravacycline) and the control group (tigecycline). The statistical hypotheses are as follows: H_0_: P1/P2 ≥ R0 (the all-cause mortality rate of the experimental group is lower than or equal to that of the control group); H_1_: P1/P2 = R1 < R0 (the all-cause mortality rate in the experimental group is greater than that in the control group). The main efficacy indicator is the comparison of the all-cause mortality rate, which is a qualitative indicator and will be analyzed using the Pearson X^2^ test or Fisher’s exact probability method.

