## Statistics

11

This study is a randomized controlled clinical trial. The two groups are the eravacycline group and the tigecycline group, with a ratio of 1:1. All-cause 30-day mortality is the main outcome measure. The researchers plan to use noninferiority tests for the ratio of two propositions to estimate the required sample size, assuming a noninferiority ratio of 2. Owing to the lack of randomized clinical trials in this specific field, sample size estimates were obtained from Xavier Guirao et al.’s observational study on the treatment of intra-abdominal infections with TGC (16). In their study, the all-cause mortality of patients treated with TGC (our control group) was 18.7%. Our previous results revealed that the mortality rate of the eravacycline group (17.7%) was slightly lower than that of the tigecycline group, with an estimated actual ratio of 0.95. The total sample size calculated through PASS (version 15.0.5) is N = 262 cases to perform a unilateral analysis *α*, achieving 80% efficacy at a level of 0.025. Considering a 10% dropout rate, the total number of subjects required for the last two groups is 292, with at least 146 subjects in each group. In light of the considerable variability observed in ICU mortality rates, an interim analysis will be conducted once 50% of the data has been collected. This analysis will facilitate a reassessment of the effect sizes and power of the study. If the initial mortality rates diverge significantly from the anticipated estimates, the sample size will be adjusted accordingly to ensure the integrity and statistical power of the study are maintained.

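### The verbal descriptions of the primary hypotheses in section 11.1 run opposite to the printed formulas and leave out the noninferiority margin of 2

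*Protocol article*

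**What the plan says.** Section 11 (Statistics) fixes the design. The endpoint is mortality, so a lower rate is better: "All-cause 30-day mortality is the main outcome measure". The sample size rests on "noninferiority tests for the ratio of two propositions to estimate the required sample size, assuming a noninferiority ratio of 2". For the control arm, "the all-cause mortality of patients treated with TGC (our control group) was 18.7"%. For the experimental arm, "the mortality rate of the eravacycline group (17.7%) was slightly lower than that of the tigecycline group, with an estimated actual ratio of 0.95". The result is "N = 262 cases to perform a unilateral analysis *α*, achieving 80% efficacy at a level of 0.025", raised to 292 for 10% dropout.

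Section 11.1 (Analysis of the main effectiveness results) then states the primary hypotheses, each as a formula followed by an explanation in parentheses:

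- H0: P1/P2 ≥ R0, explained as "the all-cause mortality rate of the experimental group is lower than or equal to that of the control group".
- H1: P1/P2 = R1 < R0, explained as "the all-cause mortality rate in the experimental group is greater than that in the control group".

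Section 11.1 does not define P1, P2, R0 or R1, and it does not mention noninferiority. No other part of the article restates or corrects these hypotheses.

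**The concern.** A ratio at or above R0 means high mortality on the numerator arm, and a ratio below R0 is the favourable side. The explanation of H0 describes low eravacycline mortality, and the explanation of H1 describes high eravacycline mortality, so both are reversed. Both also use equality of the two arms as the boundary instead of the margin.

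This is the article's only statement of the primary hypotheses, and the endpoint is death. Under the formulas, the new drug must earn its claim by ruling out a doubling of mortality. Under the words, the starting assumption is that the new drug is no worse, and the data would have to overturn it. A non-significant result could then be taken as support for eravacycline, and a small or noisy trial would make that outcome more likely.

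**Working it through.** **Step 1. Identify the symbols.** Section 11 gives 17.7% for eravacycline, 18.7% for tigecycline and a ratio of 0.95. Since 0.177/0.187 = 0.947, P1 is eravacycline and P2 is tigecycline. The opposite assignment gives 0.187/0.177 = 1.06, which does not fit. R1 is therefore 0.95, and R0 is the noninferiority ratio of 2.

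**Step 2. Reproduce the plan's sample size from the formulas.** The Farrington-Manning score test for a ratio of two proportions, with 1:1 allocation, gives

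n per arm = [(z₀.₉₇₅·s0 + z₀.₈₀·s1) / (P1 − R0·P2)]²

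- P2 = 0.187; P1 = 0.95 × 0.187 = 0.17765; P1 − 2·P2 = −0.19635.
- The constrained estimates under H0 are 0.2370 (eravacycline) and 0.1185 (tigecycline).
- s0 = √[0.2370 × 0.7630 + 4 × 0.1185 × 0.8815] = 0.7737.
- s1 = √[0.17765 × 0.82235 + 4 × 0.187 × 0.813] = 0.8685.
- n = [(1.960 × 0.7737 + 0.8416 × 0.8685) / 0.19635]² = 130.996, so 131 per arm and 262 in total, as stated.
- Dropout: 262/0.9 = 291.1, so 292, as stated.

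Other versions at one-sided 0.025 come close but do not match: 260 with P1 = 0.177, 308 with unpooled variance, and 256 on the log-ratio scale. The trial was sized on the printed formulas with R0 = 2.

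**Step 3. Set words against formulas.**

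| | Formula, with R0 = 2 | What it means | What the words say |
|---|---|---|---|
| H0 | P1/P2 ≥ 2 | eravacycline mortality at least double | eravacycline no higher than control |
| H1 | P1/P2 < 2, planned at 0.95 | eravacycline mortality less than double | eravacycline higher than control |

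The planning value of 0.95 lies inside H1. The words describing H1 say mortality is higher on eravacycline, yet the planned rates are 17.7% against 18.7%.

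**Step 4. What rejection means under the formulas.** By exact enumeration with 131 per arm and 18.7% control mortality, the score test rejects H0 with probability 0.027 at a true ratio of 2, 0.76 at a ratio of 1 and 0.81 at a ratio of 0.95. Rejection therefore supports noninferiority.

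**Step 5. The two readings at the same true ratios.** The setting is again 131 per arm and 18.7% control mortality, by exact enumeration. The verbal version is represented by a two-sided 0.05 Pearson chi-square test of equality.

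| True ratio | Words: no significant excess | Formulas: noninferiority claimed |
|---|---|---|
| 1.25 | 85% | 50% |
| 1.5 | 57% | 25% |
| 2 | 7.3% | 2.7% |

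**The case against.** The strongest reply is that the intended direction can be recovered. Section 11 states noninferiority, a margin of 2, an expected ratio of 0.95 and one-sided 0.025. The formulas agree with all of this, and 262 and 292 are reproduced. Only two parentheses are wrong, and no computed figure changes. All of that stands, and it limits the point to the statement of the hypotheses.

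A reader might infer that the trial report would announce greater mortality on eravacycline if H0 were rejected. The documents do not support that. No section states a success or reporting rule built on the verbal descriptions, and section 11 promises confidence intervals for all endpoints, which would expose such a misstatement. Misreading is a possibility that follows from the literal text, and no more.

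A reader might also set the 57% and 85% against the 2.5% error rate of the intended test. That comparison is unfair, because the 2.5% applies at a true ratio of 2. Matched at that ratio, the figures are 7.3% and 2.7%. Ratios of 1.25 and 1.5 also lie inside the plan's own margin, so a noninferiority claim there is not a false claim by the design's standard.

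Finally, section 11.1 names an ordinary Pearson or Fisher test. That does not test the ratio against 2, whichever way the words run. It is a separate issue, and the verbal-version percentages partly reflect that choice of test.

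What the reply does not remove is the contradiction itself, in the only place where the primary hypotheses are stated.

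**Conclusion.** Wrong as written. The descriptions of H0 and H1 contradict the printed formulas and the noninferiority design in section 11, and they replace the margin of 2 with a boundary of 1. The conclusion rests on reading P1 as eravacycline, P2 as tigecycline and R0 as 2. Section 11.1 does not say so, but the ratio of 0.95 and the exact match to 262 leave no plausible alternative.

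The error is one of wording and has no effect on the sample size. Its potential size, if the words were followed, is the matched comparison above: 85% against 50%, 57% against 25%, and 7.3% against 2.7% at true ratios of 1.25, 1.5 and 2. Those figures assume 18.7% control mortality, 131 evaluable patients per arm and the tests named in the working. They describe the literal text and do not predict what the sponsor will do.

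**What to change.** Replace the hypotheses in section 11.1 with:

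- H0: P1/P2 ≥ 2 (30-day all-cause mortality on eravacycline is at least twice that on tigecycline; inferior).
- H1: P1/P2 < 2 (less than twice; noninferior).
- P1 = eravacycline, P2 = tigecycline, R0 = 2, one-sided alpha 0.025; sample size computed at R1 = 0.95.

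Add one sentence saying that rejecting H0 shows a mortality ratio below 2 and does not by itself show lower mortality on eravacycline. Exchanging the two existing descriptions would correct the direction but would still leave out the margin, and would present a noninferiority result as lower mortality.

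The cost is a text correction in the protocol, best made before unblinding; 262 and 292 stay as they are. The analysis plan is not shown, so whether it repeats the wording is unknown; check it at the same time. The choice of test in section 11.1 needs its own correction so that the analysis addresses the restated hypotheses.

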## Abstract

**Background:**

Complicated intra-abdominal infections (cIAIs), often caused by multidrug-resistant bacteria such as carbapenem-resistant *A. baumannii* (CRAB) and carbapenem-resistant Enterobacteriaceae (CRE) are a critical challenge in ICUs. Owing to their high mortality and treatment failure rates, there is an urgent need for effective therapies. This trial will compare eravacycline to tigecycline for treating cIAIs in patients in the ICU, aiming to provide a superior treatment option.

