The intention to improve treatment will be analyzed based on microbiology, including all randomized subjects, who will be evaluated within their randomized groups. For continuous numerical variables, the quantity, mean, median, standard deviation, minimum, maximum, and coefficient of variation (CV, if applicable) will be determined after an independent sample t test or Wilcoxon rank sum test. The categorical variables will be reported as rates (percentages) and will be analyzed using the Pearson X^2^ test or Fisher’s exact probability method. The baseline will be defined as the last nonmissing observation data collected before the first use of the study drug. The Shapiro–Wilk test and QQ plot in SAS will be used to check the normality of the data. All the statistical analyses will be performed using SAS software (version 9.1 or higher; SAS Institute), and all the statistical inferences will be conducted using a two-sided test with a statistical significance level of 0.05. Confidence intervals (CIs) will be calculated and reported for all endpoints, thereby providing a comprehensive interpretation of the clinical relevance and statistical significance of the findings. Missing data will be classified as response uncertainty, and in the analysis of the microbiological intention-to-treat population, this will be considered treatment failure.

We will calculate and report CIs for all secondary endpoints, such as treatment response rates, to provide a comprehensive interpretation of the clinical relevance and statistical significance of our findings.

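### Section 11.1 names a Pearson/Fisher test that ignores the noninferiority ratio of 2, so the stated 80% power does not belong to it, and no stated rule leads to a noninferiority conclusion

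*Protocol article*

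**What the plan says.** **Sizing (Statistics, section 11).** "The researchers plan to use noninferiority tests for the ratio of two propositions to estimate the required sample size", "assuming a noninferiority ratio of 2". The control rate comes from an observational study in which "the all-cause mortality of patients treated with TGC (our control group) was 18.7"%. From the investigators' own results, "the mortality rate of the eravacycline group (17.7%) was slightly lower than that of the tigecycline group", with an assumed true ratio of 0.95. The level is one-sided 0.025, power is 80% and N = 262, raised to 292 (146 per group) for 10% dropout.

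**General rules (same section).** "all the statistical inferences will be conducted using a two-sided test with a statistical significance level of 0.05". Confidence intervals are promised for every endpoint.

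**Primary analysis (section 11.1).** The hypotheses in symbols are H0: P1/P2 ≥ R0 and H1: P1/P2 = R1 < R0. In words, H0 is described as experimental mortality no higher than control, and H1 as experimental mortality higher than control. The purpose is given as evaluating a difference. The method is: "The main efficacy indicator is the comparison of the all-cause mortality rate, which is a qualitative indicator and will be analyzed using the Pearson" chi-square or Fisher's exact test. Section 11.1 gives no value for R0.

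**The concern.** The sizing and the symbols describe a noninferiority question: can a mortality ratio of 2 or more be ruled out? The named test asks whether the two mortality rates differ. These are different questions with different null hypotheses. A non-significant result from the named test does not rule out a ratio of 2, and a significant one speaks to superiority or inferiority, not to the margin.

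The verbal hypotheses add to the problem. Read literally, they make rejection of H0 a finding that eravacycline has higher mortality, which is the reverse of the symbols.

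Three things are at stake for a mortality endpoint: which claim the trial will make, whether the rule for making it is fixed before the data are seen, and what power means when it is reassessed at the planned interim analysis.

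**Working it through.** **Inputs (Statistics, section 11).** P2 = 0.187; R1 = 0.95, so P1 = 0.95 × 0.187 = 0.17765 (the text rounds this to 17.7%); R0 = 2; one-sided α = 0.025, z = 1.960; power 80%, z = 0.8416; allocation 1:1.

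**1. Reproduce the plan's N.** Farrington-Manning score test for a ratio:

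n per arm = [z(0.975)·s0 + z(0.80)·s1]² / (R0·P2 − P1)²

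- Rates restricted to P1/P2 = 2: 0.23696 and 0.11848.
- s0 = √[0.23696 × 0.76304 + 4 × 0.11848 × 0.88152] = 0.7737
- s1 = √[0.17765 × 0.82235 + 4 × 0.187 × 0.813] = 0.8685
- R0·P2 − P1 = 0.374 − 0.17765 = 0.19635
- n = [(1.960 × 0.7737 + 0.8416 × 0.8685) / 0.19635]² = [(1.5164 + 0.7309) / 0.19635]² = 130.996, so 131 per arm.

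The total is 262, which matches the plan. Dropout: 262 / 0.9 = 291.1, giving 292 (146 per arm), which also matches. The 80% therefore belongs to a test against a ratio of 2.

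**2. Chance that the named test is significant.** This sums the two binomial distributions over all tables that are significant at two-sided 0.05, with P1 = 0.17765 and P2 = 0.187.

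| Per arm | Chi-square | of which favouring eravacycline | Fisher |
|---|---|---|---|
| 131 | 5.4% | 3.9% | 3.8% |
| 146 | 5.5% | 4.0% | 3.9% |

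**3. Size that the named test would need for 80% power.**

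n = [1.960·√(2p̄(1−p̄)) + 0.8416·√(P1(1−P1) + P2(1−P2))]² / (P1 − P2)², where p̄ is the mean of P1 and P2.

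- 17.7% vs 18.7%: [(1.960 × 0.54567 + 0.8416 × 0.54562) / 0.010]² ≈ 23,370 per arm.
- 17.765% vs 18.7%: [(1.960 × 0.54605 + 0.8416 × 0.54601) / 0.00935]² ≈ 26,770 per arm.

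The answer moves by several thousand with the rounding of P1, so each figure should be quoted with its own rates.

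**4. Power of a rule that uses the margin.** The same enumeration with P1 = 0.17765:

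| Per arm | Score test against 2, one-sided 0.025 | Upper limit of log-ratio 95% CI below 2 |
|---|---|---|
| 131 | 80.6% | 80.3% |
| 146 | 84.3% | 84.0% |

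**5. Why non-significance does not settle the question.** Two illustrative results with 131 per arm, using ratio × exp(±1.96·√(1/a − 1/131 + 1/b − 1/131)), where a and b are the deaths on eravacycline and tigecycline:

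- 24 vs 24 deaths: ratio 1.00, 95% CI 0.60 to 1.67, chi-square p = 1.00.
- 32 vs 24 deaths: ratio 1.33, 95% CI 0.83 to 2.13, chi-square p = 0.23.

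The named test gives the same answer to both, not significant. Only the first excludes a ratio of 2.

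**The case against.** **The ingredients of a noninferiority analysis are already there.** The symbols in 11.1 have the right form, the Statistics section gives the ratio of 2, and confidence intervals are promised for all endpoints. A log-ratio interval read against 2 has about 80% power at 131 per arm. This largely stands. A reader might infer that the trial could never declare noninferiority, or that 11.1 sets out only a test of equality. The document does not support either. What it lacks is any sentence linking an interval to the margin, while the test it does name leaves the margin out.

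**One-sided 0.025 and two-sided 0.05 are not in conflict.** This stands. Reading the upper limit of a two-sided 95% interval is a one-sided 0.025 test. The fault is the missing margin, not the sidedness.

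**A separate analysis plan may settle it, and an article condenses.** This does not remove the point. The protocol does not leave the primary test open. It names one, and an analysis plan that used a margin-based test would contradict it.

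**The Abstract's aim shows that superiority was intended.** A reader might infer this from "aiming to provide a superior treatment option". That phrase is background motivation, not a hypothesis, and the sizing is plainly for noninferiority.

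**A non-significant result would be taken as success.** A reader might fear this, but the document sets no such rule. It sets no noninferiority rule of any kind, and that is the defect.

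**Conclusion.** The point holds as a contradiction within the protocol. The sample size is arithmetically right for a noninferiority test of the mortality ratio against 2, and the symbols in 11.1 agree with it. The verbal hypotheses and the named test do not. At the planning rates the named chi-square test is significant about 5.4% of the time at 131 per arm, not 80%, and as ordinarily run it cannot reject P1/P2 ≥ 2. No stated rule permits a noninferiority conclusion.

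This rests on three assumptions: Pearson and Fisher are run in their usual form, with equality as the null; R0 in 11.1 is the ratio of 2 from the Statistics section; and the planning rates are the protocol's own. A reader might infer that the trial is too small. That does not follow, because N = 262 is adequate for the test it was calculated for. Whether a ratio of 2 (37.4% against 18.7% mortality) is an acceptable margin is a separate question, not judged here. The correction should be made before mortality data are seen, because a decision rule chosen afterwards would be post hoc.

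**What to change.** In section 11.1:

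- State R0 = 2.
- Replace the Pearson/Fisher test as the primary analysis with a score test (Farrington-Manning/Miettinen-Nurminen) of P1/P2 against 2 at one-sided 0.025. Equivalently, declare noninferiority if the upper limit of the two-sided 95% score confidence interval for the mortality ratio is below 2.
- Allow a superiority claim only if that upper limit is below 1.
- Rewrite the verbal hypotheses to match the symbols: H0, experimental mortality is at least R0 times control mortality; H1, it is less than R0 times control mortality.
- Describe the purpose as a noninferiority comparison.

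The general sentence on two-sided tests at 0.05 can stay if the interval rule is adopted. The cost is wording in the protocol, and in the analysis plan if there is one. N stays at 262, or 292 with dropout, and no further patients or data are needed.

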### Analysis of secondary effectiveness results

11.2

The Pearson X^2^ test or Fisher’s exact probability method will be used to compare the differences between the two groups at different visit times and the proportion of total-response patients in different analysis populations. The length and cost of ICU hospitalization will be evaluated using independent sample t tests or Wilcoxon rank sum tests.

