## Effectiveness evaluation

8

The primary efficacy end point is the all-cause 30-day mortality of patients in clinically evaluable and microbiologically evaluable populations.

The secondary efficacy endpoints are as follows: (1) the proportion of patients with a total response (composite endpoint consisting of clinical cure and microbiological response) in the clinically evaluable population at the end of treatment (days 5–14) and the test of cure visits (days 12 ± 2); (2) the proportion of total responsive patients in the microbiome-evaluable population at the end of treatment and the test of cure visits; (3) the proportion of microbiologically evaluable patients in the population with a total response to each pathogenic bacterium at the end of treatment and the test of cure visits; (4) the total response proportion of patients with drug-resistant bacterial infections in the microbiome-evaluable population at the end of treatment and the test of cure visits; (5) ICU hospitalization time and expenses; (6) quality of life outcomes or functioning after ICU discharge as assessed by application of the EuroQol-5D and Barthel Index scales; (7) changes in Sequential Organ Failure Assessment (SOFA) scores, reflecting the impact of the treatment on organ dysfunction over time; and (8) time to clinical improvement, measured from the start of treatment until the first observation of significant improvement in clinical status.

Given the variable susceptibility of MDR pathogens to tetracyclines, our study protocol will include analyses stratified by bacterial species. Specifically, subgroup analyses will be conducted for CRAB and CRE to gain a deeper understanding of the comparative efficacy of eravacycline versus tigecycline.

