Outcome data	Survival at 30 days post randomization Date of death or discharge Total response (composite endpoint consisting of clinical cure and microbiological response) at the end of treatment and the test of cure visits Length of ICU stay and costs Protocol violations and adverse events Reasons for trial withdrawal

cIAI, complicated intra-abdominal infection; ICU, intensive care unit; APACHE, Acute Physiology and Chronic Health Evaluation; SOFA, Sequential Organ Failure Assessment; CRP, C-reactive protein; PCT, procalcitonin.

An independent Data Safety and Monitoring Board (DSMB) will be constituted to further enhance the safety and integrity of the study. The DSMB, comprising experts with pertinent knowledge and experience, will operate independently of the study team. Its remit is to conduct regular reviews of the accumulating trial data, to ensure the safety of participants and the validity of the trial results. The DSMB will have the authority to recommend to the sponsor whether to continue, modify, or stop the trial, based on its data review insights.

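### ICU length of stay is compared with no stated rule for deaths, so an early death counts like an early recovery; the distortion is small at planned mortality, and its direction depends on when deaths occur

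*Protocol article*

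**What the plan says.** Section 8 (Effectiveness evaluation) places "5) ICU hospitalization time and expenses" among eight secondary efficacy endpoints, without further definition. Section 11.2 fixes the analysis: "The length and cost of ICU hospitalization will be evaluated using independent sample t tests or Wilcoxon rank sum tests". Table 3 (section 10) collects "Length of ICU stay and costs" and also "Survival at 30 days post randomization Date of death or discharge"; it lists ICU admission time and the date and time of randomization as well.

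Section 11 (Statistics) gives the expected mortality. For the control, "the all-cause mortality of patients treated with TGC (our control group) was 18.7" percent; for the experimental arm, "the mortality rate of the eravacycline group (17.7%) was slightly lower than that of the tigecycline group", "with an estimated actual ratio of 0.95". The sample size is computed "assuming a noninferiority ratio of 2".

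The article states no rule for deaths in the stay or cost variable: no composite, no worst rank, no competing event. The one missing-data rule in section 11 concerns response only. Section 4.4 lists death as an exit criterion without saying what that means for this endpoint.

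**The concern.** A patient who dies in the ICU on day 3 and one who recovers and leaves on day 3 have the same length of stay. A t test or Wilcoxon test on the observed stay treats them alike, and a shorter stay on an efficacy list is read as benefit. If mortality is equal in the two arms, this does little harm. If it differs, part of the difference in stay is only the difference in deaths, carried over with a sign set by whether those who die leave the ICU sooner or later than survivors. Mortality is the primary endpoint, so a difference in deaths is exactly what the trial is looking for. A secondary efficacy measure that may move in either direction when deaths rise cannot be interpreted beside it.

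**Working it through.** **Inputs from the protocol article.** Control mortality 18.7%, experimental mortality 17.7%, assumed ratio 0.95, noninferiority ratio 2, one-sided alpha 0.025, power 80%, 10% dropout, 146 per arm (section 11).

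**Assumed inputs.** The documents give no stay by survival status. Base assumption: 12 days for survivors and 6 for those who die, the same in both arms. For simplicity all 30-day deaths are taken to occur in the ICU; deaths after ICU discharge would shrink the artefact.

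**1. The plan's own figure.** Score test for a ratio of two proportions (Farrington-Manning), with p2 = 0.187, p1 = 0.95 × 0.187 = 0.1777 and R0 = 2. Under the null the constrained rates are 0.2370 and 0.1185.
- s0 = √(0.2370 × 0.7630 + 4 × 0.1185 × 0.8815) = 0.774
- s1 = √(0.1777 × 0.8223 + 4 × 0.187 × 0.813) = 0.868
- n per arm = (1.960 × 0.774 + 0.842 × 0.868)² / (0.374 − 0.1777)² ≈ 131, total 262
- 262 / 0.9 = 291.1, so 292 with equal arms

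Both stated totals reproduce, so this test is used below to decide what would be declared noninferior.

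**2. Expected deaths.** 146 × 0.177 = 25.8 and 146 × 0.187 = 27.3. Together 53.1 / 292 = 18.2%.

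**3. Size of the artefact.** With identical stays within survivors and within decedents, the difference in mean stay (experimental minus control) is (mE − mC) × (decedents' stay − survivors' stay).

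| Mortality, experimental v control | Mean stay at 12/6 days | Difference |
|---|---|---|
| 17.7% v 18.7% (planned) | 10.94 v 10.88 | +0.06 day |
| 34/146 v 27/146 (23.3% v 18.5%) | 10.60 v 10.89 | −0.29 day |
| 37.4% v 18.7% | 9.76 v 10.88 | −1.12 days |

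**4. Where noninferiority stops.** With 146 per arm and 27 control deaths, the score statistic is −2.02 at 34 experimental deaths (passes) and −1.91 at 35 (fails). The largest observed ratio that passes is therefore 34/27 = 1.26. With 131 per arm and 24 control deaths the limit is 29 (ratio 1.21), and the artefact is 5/131 × 6 = 0.23 day. If true mortality were 37.4% v 18.7%, noninferiority would be declared about 2.7% of the time.

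**5. Sensitivity to the assumed stays.** With survivors at 14 days and mortality of 37.4% v 18.7%, the difference is −1.31 days if decedents stay 7 days, −1.87 if 4, zero if 14 and +1.12 if 20. The sign is set by the timing of deaths.

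**6. Chance of a significant result when survivors' stays are identical.** Simulation with 146 per arm, 1,500 runs per scenario, lognormal stays with log-SD 0.7, survivors' mean 14 days and decedents' mean 7 or 4 days:
- 17.7% v 18.7%: about 5% for both tests, the nominal level
- 25% v 18.7%, just beyond the noninferiority limit: 6–7% (t test), 7–12% (Wilcoxon)
- 37.4% v 18.7%: 22–36% (t test), 31–62% (Wilcoxon)

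**7. A death-aware measure.** Mean ICU-free days to day 30, with death scored 0, is (1 − m) × (30 − 12). This gives 14.8 v 14.6 at the planned rates, 13.8 v 14.7 at 34 v 27 deaths, and 11.3 v 14.6 at 37.4% v 18.7%. The arm with more deaths is worse each time, whenever the deaths occur.

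**The case against.** The main counter-argument is about size, and much of it stands. A reader might infer from the margin of 2 that an arm with doubled mortality could be called noninferior while appearing 1.1 days better on ICU stay. The documents do not support that: the margin bounds the true ratio, and an observed ratio above about 1.26 fails (step 4). Observed mortality near 37.4% v 18.7% would also give p < 0.001 on the chi-square test named in section 11.1, so harm would be plain on the primary endpoint. At the planned rates the artefact is negligible.

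A reader might also infer that the arm with more deaths will necessarily look shorter and cheaper. That requires deaths to come before survivors' discharge, which the documents do not show. Section 4.2 excludes patients with short expected survival, which should remove some very early deaths.

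On cost, a reader might conclude that the planned test is invalid. It is not: mean cost incurred per randomised patient is a legitimate resource quantity that already includes patients who die, and a t test compares exactly that mean. The weakness lies only in reading lower cost as efficacy.

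Finally, this is a condensed article, and the construction of the stay variable could be set out in a fuller document; that the test applies to stay as observed is inferred from the absence of any other definition. This limits the severity. But the article does commit to a test for a named efficacy endpoint and lists the outcome simply as length of ICU stay, so the definition should be settled explicitly.

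**Conclusion.** The point holds at moderate weight. The planned comparison of ICU stay has no stated account of death, with about 18% of patients expected to die, so its result has no fixed clinical meaning if mortality differs between arms. On assumed stays of 12 and 6 days, the distortion is about 0.06 day at planned mortality and about 0.3 day at the largest observed excess of deaths compatible with a noninferiority claim (146 per arm, 27 control deaths, score test). It reaches about 1.1 days only at 37.4% v 18.7%, where noninferiority would not be declared. The sign depends on the timing of deaths, which is not documented. The absence of a rule is certain on the text of the article; the size and direction rest on the assumptions above. The primary endpoint and the sample size are unaffected.

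**What to change.** In section 11.2, replace the comparison of observed ICU stay by one of:
- ICU-free days from randomization to day 30, with death by day 30 scored 0 (or ranked worst), compared by the Wilcoxon test already named; or
- time to ICU discharge alive, with death as a competing event.

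Beside either, show 30-day survival and survivors' ICU stay separately. Keep mean cost per randomised patient, but present it next to mortality as resource use, and state that lower cost will not be read as evidence of efficacy.

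The cost is a change of wording. Table 3 already holds randomization time, ICU admission time, length of ICU stay, 30-day survival and date of death or discharge; it need only be made clear that the ICU discharge date can be derived from these. No extra patients or visits are needed. One small downside: ICU-free days mix survival and stay, so a difference could come from either, which is why both parts must be shown.
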